## Statistical analysis

All analyses will be performed after the study is completed and the database is released. All statistics, including tables, figures and listings, will be performed using R version >3.5. Men creating referral before 2020-01-09 are included in main analysis. All participants with will be followed a minimum of 200 days after receiving the result from their blood sample (PSA and Stockholm3 score). In addition, biopsied men will be followed at least 30 days post-biopsy to monitor adverse events, and participants undergoing radical prostatectomy prior to database lock will be followed until pathology results from the prostatectomy are available.

### Study populations

1. *ITT population* includes all men who:
  - a. signed the written informed consent to participate in the study,
  - b. fulfilled all inclusion criteria and none of the exclusion criteria,
  - c. were randomised to either study arm.

Conditions for excluding patients from the ITT population, based on deviations from the study protocol:

| Randomisation arm | MRI           | No biopsy | SBx only | TBx only | SBx and TBx |
|-------------------|---------------|-----------|----------|----------|-------------|
| Standard arm      | MRI or no MRI | Include   | Include  | Include  | Include     |
| Experimental arm  | MRI or no MRI | Include   | Include  | Include  | Include     |

Randomised allocation and analysis group for ITT analyses:

| Randomisation arm | Test received                           | Analysis group   |
|-------------------|-----------------------------------------|------------------|
| Standard arm      | Systematic biopsy (with or without MRI) | Standard arm     |
| Standard arm      | Targeted biopsy                         | Standard arm     |
| Standard arm      | Systematic biopsy and Targeted biopsy   | Standard arm     |
| Standard arm      | No biopsy / Other                       | Standard arm     |
| Experimental arm  | Systematic biopsy (with or without MRI) | Experimental arm |
| Experimental arm  | Targeted biopsy                         | Experimental arm |

|                  |                                       |                  |
|------------------|---------------------------------------|------------------|
| Experimental arm | Systematic biopsy and Targeted biopsy | Experimental arm |
| Experimental arm | No biopsy / Other                     | Experimental arm |

2. *PP population* includes men who:

- a. are included in the ITT population,
- b. have a valid PSA value and Stockholm3 score,
- c. have a complete systematic pathology report if randomised to standard arm (but no targeted pathology report),
- d. have a complete MRI report if randomised to experimental arm and (i), (ii), or (iii), as appropriate,
  - i. have a complete systematic and a complete targeted pathology report if PIRADS $\geq$ 3,
  - ii. have a complete systematic pathology report if PIRADS $<$ 3 and Stockholm3 $\geq$ 25% (but no targeted pathology report),
  - iii. did not undergo any biopsy if PIRADS $<$ 3 and Stockholm3 $<$ 25%.

Conditions for excluding patients from the PP population, based on deviations from the study protocol:

| Randomisation arm | Further specifications                     | No biopsy | SBx only | TBx only | SBx and TBx |
|-------------------|--------------------------------------------|-----------|----------|----------|-------------|
| Standard arm      | No MRI                                     | Exclude   | Include  | Exclude  | Exclude     |
| Standard arm      | MRI                                        | Exclude   | Exclude  | Exclude  | Exclude     |
| Experimental arm  | No MRI                                     | Exclude   | Exclude  | Exclude  | Exclude     |
| Experimental arm  | MRI PIRADS $\geq$ 3                        | Exclude   | Exclude  | Exclude  | Include     |
| Experimental arm  | MRI PIRADS $<$ 3 and Stockholm3 $\geq$ 25% | Exclude   | Include  | Exclude  | Exclude     |
| Experimental arm  | MRI PIRADS $<$ 3 and Stockholm3 $<$ 25%    | Include   | Exclude  | Exclude  | Exclude     |

The analyses will be performed and reported on both the ITT and PP population.

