### Key secondary endpoints

| Variable                                   | Measure | Comment                        |
|--------------------------------------------|---------|--------------------------------|
| Non-clinically significant prostate cancer | Yes/No  | ISUP = 1                       |
| Biopsy performed                           | Yes/No  | Any biopsy procedure performed |
| MRI performed                              | Yes/No  | MR procedure performed         |

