| 0.020 | 0.61 | 0.67 |
| 0.025 | 0.61 | 0.77 |
| 0.030 | 0.61 | 0.84 |
| 0.015 | 0.63 | 0.59 |
| 0.020 | 0.63 | 0.71 |
| 0.025 | 0.63 | 0.80 |
| 0.030 | 0.63 | 0.87 |

2. More than 90% power for the contrast PSA+MRI+TBx+SBx vs PSA+SBx (rDP = 1.3, noninferiority margin for  $\Delta DP \delta = 0.04$ ,  $\alpha = 0.025$ ).

Thus, contrast 1 drives the required samples size of the study. We therefore powered the study (with respect to sample size for sending out invitations and enrolling participants) to have sufficient statistical power to answer comparisons of Stockholm3 vs. PSA within the experimental arm.

Note: no correction for multiple comparisons was made. This means that each of the three tests (with respect to the ISUP 2, ISUP 1, and biopsy endpoints) has an approximate type I error rate of 2.5% if the corresponding null hypothesis is true. If all three null hypotheses are true and we assume the tests to be independent, the overall type I error rate is approximately 7%. In reality however, these hypotheses are strongly correlated. Thus, the overall type I error rate is bounded below by 2.5% and above by 7%.

R code for the power calculations is available at:

<https://gist.github.com/anddis/fc1a265d102b509b0eacd59ab065661a>

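### In the PP population, the between-arm comparison of Biopsy performed is decided by the PP inclusion rule, so its sign is fixed and its 2.5% error rate does not hold

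*Combined protocol and SAP*

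**What the plan says.** The SAP lists *Biopsy performed*, defined as "Any biopsy procedure performed", under Key secondary endpoints. Fewer biopsy procedures are also part of the overarching primary hypothesis and the primary aim. The multiplicity note under Updated sample size calculations gives a false-positive rate of about 2.5% for "each of the three tests (with respect to the ISUP 2, ISUP 1, and biopsy endpoints").

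Under Study populations, three PP conditions matter here:

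- Standard-arm men must "have a complete systematic pathology report if randomised to standard arm (but no targeted pathology report"). The exclusion table marks standard-arm men without a biopsy as excluded.
- Experimental-arm men must "have a complete systematic and a complete targeted pathology report if PIRADS" ≥3. With PI-RADS <3 and Stockholm3 ≥25% they need a complete systematic report.
- The remaining experimental-arm men, with Stockholm3 <25%, stay only if they "did not undergo any biopsy if PIRADS" <3.

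The section closes with "The analyses will be performed and reported on both the ITT and PP population". Neither population is named as primary for any endpoint. Under Contrasts between study arms, contrasts 3v1, 2v1 and 9v7 are analysed as absolute differences and 6v1 and 5v1 as ratios, with Wald intervals.

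**The concern.** For this endpoint a man without a biopsy has a known outcome, which is no. The PP rule removes him from the control arm because of that outcome. It also removes MRI-negative men below the 25% threshold who were biopsied off protocol. These are the men whose data could count against a claim of fewer biopsies. What remains is 100% in control against the share of retained experimental-arm men whom the algorithm sends to biopsy. The comparison restates the algorithm and says little about biopsies actually done.

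Two things are at stake. A PP test would be reported at a nominal 2.5% error rate that it does not have. And the absolute biopsy saving would be quoted as larger than the one among randomised men.

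**Working it through.** **1. The plan's own figures.** Three independent tests at 0.025 give 1 − (1 − 0.025)³ = 0.0731, which agrees with "the overall type I error rate is approximately 7" per cent. The flow also reproduces: 12,500 × 0.13 = 1,625, or about 1,600 randomised men with PSA ≥3, which at 2:3 is 640 control and 960 experimental.

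**2. The PP proportions.** In control every retained man is biopsied, so the proportion is 1. Its Wald term is 1 × (1 − 1)/n = 0 on the absolute scale and 1/(1 × n) − 1/n = 0 on the log-ratio scale. In the experimental arm let A be retained men with PI-RADS ≥3 or Stockholm3 ≥25% (all biopsied), and B be retained men with PI-RADS <3 and Stockholm3 <25% (none biopsied). The proportion is A/(A + B), so the difference is −B/(A + B), which is never above zero.

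**3. How few men decide the test.** With N = A + B and B = 4, z = (4/N) ÷ √[(4/N)(1 − 4/N)/N] = 2/√(1 − 4/N). This exceeds 2, and so 1.96, at any N. With B = 3 and N = 200, z = 1.75. On the ratio scale with N = 200 and B = 4, the upper log limit is log(0.98) + 1.96 × √(1/196 − 1/200) = −0.0004, which also rejects.

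**4. The plan's assumptions.** The protocol addendum gives 20% not following protocol and 55% MRI-negative. I take the 20% as unbiopsied in both arms and first ignore MRI-negative men with Stockholm3 ≥25%, whose share the documents do not give.

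- ITT: control 0.80, experimental 0.80 × 0.45 = 0.36. Difference −44 points, ratio 0.36/0.80 = 0.45.
- PP: control 1.00, experimental 0.45. Difference −55 points, ratio 0.45.

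If 15% of MRI-negative men have Stockholm3 ≥25% (assumed), the algorithm's biopsy share is 0.45 + 0.55 × 0.15 = 0.5325. ITT is then 80% against 42.6% (−37.4 points) and PP 100% against 53.25% (−46.75 points). The ratio is 0.53 in both.

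**5. Error rate when equal shares of randomised men are biopsied.** The table shows 10,000 simulated trials per row, with 640/960 men, the PP rules applied literally, and the SAP's Wald interval at one-sided 0.025.

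| Scenario | ITT control / exp. | ITT rejects | PP control / exp. | PP rejects |
|---|---|---|---|---|
| Control uptake 36% | 36% / 36% | 2.2% | 100% / 45% | 100% |
| As above, 15% of MRI-negative men at Stockholm3 ≥25% (assumed) | 42.6% / 42.6% | 2.5% | 100% / 53% | 100% |
| 77% of MRI-negative men and 50% of men without MRI biopsied (assumed) | 80% / 80% | 2.5% | 100% / 78% | 100% |
| 95% of MRI-negative men and 11% of men without MRI biopsied (assumed) | 80% / 80% | 2.6% | 100% / 94% | 100% |
| More biopsies in the experimental arm | 30% / 36% | 0.0% | 100% / 45% | 100% |

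The equal-share scenarios were repeated with MRI-negative shares of 30–70% and with arms of 840/1,260 and 415/623. ITT rejected in 2.0–2.9% of trials. The lowest PP rejection rate was 99.9%.

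**6. Uneven uptake.** Assume, for illustration, control uptake of 65%, MRI attendance of 90%, and biopsy in 95% of MRI-positive men.

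- ITT experimental: 0.90 × 0.45 × 0.95 = 0.385. Ratio to 0.65 is 0.59.
- PP experimental: (0.45 × 0.95)/(0.45 × 0.95 + 0.55) = 0.4275/0.9775 = 0.44. Ratio to 1 is 0.44.

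**The case against.** The strongest reply is that the PP contrast usually points the right way. If men comply equally well with a recommended biopsy in both arms, the MRI pathway does produce fewer biopsies. The equal-share scenarios need either much lower control compliance or many off-protocol biopsies, and neither resembles the plan's 20%. That stands. ITT keeps every unbiopsied man, is reported alongside, and shows 80% against 36% at the plan's figures.

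It is also fair that the SAP's test specifications for the primary and key secondary endpoints spell out no biopsy test. The test is inferred from the aims and the multiplicity note. The missing-data section does warn that PP assumes data missing completely at random and that dropout may be uneven. But that warning concerns missing outcomes, and here the outcome is known and decides inclusion.

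Four stronger readings are tempting and are not supported:

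- **The biopsy-reduction claim is unsafe.** ITT carries it.
- **PP always inflates the saving.** At the plan's figures the ratio is the same in both populations.
- **The trial will rest its claim on PP.** No section gives PP confirmatory status.
- **Every PP biopsy or MRI comparison is void.** Contrasts 6v3 and 5v2 lie within the experimental arm and do not use the control proportion. The artificial-randomisation analysis adds screen-negative men to the denominators, so control is no longer 100%. The stated MRI-reduction hypothesis compares Stockholm3 with PSA within the experimental arm.

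**Conclusion.** The point holds for between-arm contrasts among screen-positive randomised men (3v1, 2v1, 9v7, 6v1, 5v1), with the proportion taken given a positive screen, as in the SAP's definition of detection probability. There the PP comparison of *Biopsy performed* conditions on its own endpoint. It cannot favour control, and the stated 2.5% does not describe it: rejection is essentially certain when equal shares of randomised men are biopsied.

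The cost at the plan's assumptions is 11 percentage points on the absolute scale (55 against 44) and nothing on the ratio scale. The PP ratio overstates the reduction only if uptake is higher in the MRI arm. Additional hypothesis 5 predicts this and the missing-data section allows for it. The direction at plan assumptions is unchanged. The fixed control proportion and sign follow from the SAP's tables alone. The simulated rates also use the assumed uptake, off-protocol and Stockholm3 ≥25% shares shown.

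**What to change.** Add one sentence to Study populations: between-arm comparisons of *Biopsy performed*, and of *MRI performed* if made, are tested and claimed in the ITT population only. In PP, report the experimental-arm proportion biopsied under the algorithm descriptively (an interval is acceptable), with no between-arm test. State that the within-arm contrasts (6v3, 5v2) and the artificial-randomisation analyses stay as planned in both populations.

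The cost is SAP wording. No useful power is lost, since the ITT biopsy test rejects in about 100% of simulated trials at the plan's assumptions. The quoted absolute saving would be the ITT figure, about 11 points below the PP one at those assumptions.

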### Patients' characteristics

Patients' characteristics will be presented with descriptive statistics, overall, by study arm, and/or by screening test (positive/negative), as appropriate. Continuous variables will be summarized using measures of central tendency and variability. Categorical variables will be summarized using absolute and relative frequencies. No formal statistical testing will be performed.

### Analyses

#### *Data structure*

The table below lays out the general data structure for the STHLM3-MRI trial.

|                     |
|---------------------|
| Standard arm |
|---------------------|

|                          | Endpoint = positive (yes) |                   | Endpoint = negative (no) |                   |
|--------------------------|---------------------------|-------------------|--------------------------|-------------------|
|                          | PSA test positive         | PSA test negative | PSA test positive        | PSA test negative |
| Stockholm3 test positive | a                         | b                 | e                        | f                 |
| Stockholm3 test negative | c                         | [d]               | g                        | [h]               |
| Experimental arm  |                           |                   |                          |                   |
|                          | Endpoint = positive (yes) |                   | Endpoint = negative (no) |                   |
|                          | PSA test positive         | PSA test negative | PSA test positive        | PSA test negative |
| Stockholm3 test positive | a'                        | b'                | e'                       | f'                |
| Stockholm3 test negative | c'                        | [d']              | g'                       | [h']              |

Note: since the study protocol dictates that only those patients who screen positive on either screening test are referred for further work-up, the number of patients reported between brackets are unknown. In a standard screen-positive study, the total number of patients [d]+[h] (and [d']+[h']) is known. However, this study combines a paired and a randomised design and only those men who screen positive on either test are randomised. Therefore, the quantities [d]+[h] and [d']+[h'] are unknown in the present study.

#### *Contrasts between study arms (unpaired design)*

Analyses will compare the difference in detection probabilities (DPs) between study arms. The DP is the probability of being endpoint-positive given the study arm and, possibly, either or both screening tests being positive. For example the DP of ISUP1 in men randomised to the experimental arm and Stockholm3-positive is equal to  $\Pr(\text{ISUP1} \mid \text{Stockholm3} \geq 11\%, \text{Experimental arm})$ .

**Absolute scale.** The absolute difference in DPs is defined as the DP in the experimental arm minus the DP in the standard arm ( $\Delta\text{DP} = \text{DP}_{\text{Exp}} - \text{DP}_{\text{Std}}$ ) or vice versa, as appropriate. It is estimated by plugging into the formula the observed proportions. An approximate 100(1- $\alpha$ )% two-sided Wald confidence interval for  $\Delta\text{DP}$  is calculated as

$$\widehat{\Delta\text{DP}} \pm z_{\alpha/2} \sqrt{\frac{\widehat{\text{DP}}_{\text{Exp}}(1-\widehat{\text{DP}}_{\text{Exp}})}{n_{\text{Exp}}} + \frac{\widehat{\text{DP}}_{\text{Std}}(1-\widehat{\text{DP}}_{\text{Std}})}{n_{\text{Std}}}}.$$

**Relative scale.** The relative difference in DPs is defined as the DP in the experimental arm divided by the DP in the standard arm ( $r\text{DP} = \text{DP}_{\text{Exp}}/\text{DP}_{\text{Std}}$ ) or vice versa, as appropriate. It is estimated by plugging into the formula the observed proportions. An approximate 100(1- $\alpha$ )% two-sided Wald confidence interval for  $r\text{DP}$  is calculated as

$$\exp\left(\log(\widehat{r\text{DP}}) \pm z_{\alpha/2} \sqrt{\frac{1}{\widehat{\text{DP}}_{\text{Exp}} * n_{\text{Exp}}} - \frac{1}{n_{\text{Exp}}} + \frac{1}{\widehat{\text{DP}}_{\text{Std}} * n_{\text{Std}}} - \frac{1}{n_{\text{Std}}}}\right).$$

Contrasts 3 vs 1, 2 vs 1, and 9 vs 7 will be analysed using absolute differences (Study 1). Contrasts 6 vs 1, and 5 vs 1 will be analysed using relative differences (Study 2).

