### **13.3. Randomization**

Randomization is performed 2:3 between control arm and experimental arm.

Randomisation will be performed using stratification on disease risk (three strata). Disease risk is assessed using the Stockholm3 test.

Six allocation lists have been created, specifying the sequence of study arm allocation. Participants are first allocated to corresponding list, and then allocated to study arm

according to the order in which they participate. The allocation sequence is blinded from the study investigators and handled by the study database administrator (SDA, [name]).

In order to enhance resource usage, men are allocated to the study sites according to local availability of biopsy procedure slots.

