## 9. (PSA | S3M)+MRI+TBx+SBx,

where (PSA | S3M) denotes positive on either PSA or S3M screening tests, SBx denotes systematic biopsies, and TBx denotes targeted biopsy. To be clear, only MRI positive men (PIRADS  $\geq 3$ ) are biopsied in the strategies that include MRI (apart from men with S3M  $\geq 25\%$ ). This is true irrespective of the biopsy procedure (i.e. SBx is also only performed in MRI positive men in these strategies) (Figure 1). ***The above strategies will in the rest of this document be referred to as Strategy 1, 2, 3, 4, 5, 6, 7, 8, and 9, respectively.***

Randomization stratified on disease risk [sextiles of the Stockholm3 test] will be used. Further, block allocation will be performed, with each block consisting of five men, two of which will be randomized to systematic biopsies and three will be randomized to the MRI arm. This means that randomization guarantees a proportional number of men in each arm and with more evenly distributed characteristics in terms of disease risk and test concordance.

[figure not shown]

**Figure 1:** Overview of the STHLM3 MR Phase 2 study design. Men aged 50-74 are invited to the study from the general population. Blood is sampled from study participants and PSA as well as Stockholm3 are measured. Men with elevated prostate cancer risk (PSA  $\geq 3$  ng/ml or Stockholm3  $\geq 11\%$ ) are randomized to be referred to either systematic biopsies (control arm) or undergo MRI and targeted plus systematic biopsies in case the MRI indicates areas of the prostate suggestive of prostate cancer (PIRADS  $\geq 3$ ). The design thus combines a paired step where PSA and Stockholm3 can be compared (paired screen positive design) and a randomized step where systematic biopsies can be contrasted to MRI and subsequent targeted and systematic biopsies for MRI positive men.

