#### *Non-inferiority and superiority tests*

The null and the alternative hypothesis for a non-inferiority test for the  $\Delta DP$  are:

$$\begin{aligned} H_0: \Delta DP &\leq -\delta \\ H_a: \Delta DP &> -\delta \end{aligned}$$

where  $\delta > 0$  is the non-inferiority margin. This means that non-inferiority for a specific endpoint will be claimed if the lower boundary of the two-sided  $(2\alpha \times 100)\%$  confidence interval for the  $\Delta DP$  does not cover  $-\delta$ .

The null and the alternative hypothesis for a superiority test for the  $\Delta DP$  are:

$$\begin{aligned} H_0: \Delta DP &\leq \theta \\ H_a: \Delta DP &> \theta \end{aligned}$$

where  $\theta \geq 0$  is the superiority margin. This means that superiority for a specific endpoint will be claimed if the lower boundary of the two-sided  $(2\alpha \times 100)\%$  confidence interval for the  $\Delta DP$  does not cover  $\theta$ .

For comparisons on a relative scale (rTPF), the null and the alternative hypothesis for non-inferiority and superiority tests are

$$H_0: rDP \leq \exp(-\delta)$$

$$H_a: rDP > \exp(-\delta)$$

and

$$\begin{aligned} H_0: rDP &\leq \exp(\theta) \\ H_a: rDP &> \exp(\theta) \end{aligned}$$

respectively, with non-inferiority and superiority margins equal to  $\delta > 0$  and  $\theta \geq 0$ .

One-sided p-values will be calculated based on the test considered (non-inferiority or superiority).

Switching from non-inferiority to superiority: if the two-sided  $(2(1 - \alpha) \times 100)\%$  confidence interval for  $\Delta DP$  (rTPF) not only lies entirely above the non-inferiority margin, but also above the superiority margin, superiority will be claimed at the same alpha-level set for the non-inferiority test. In this case, we will also calculate the p-value associated with a test for superiority.

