#### *Basic data and assumptions used in the sample size calculations*

We used data from the STHLM3 trial for sample size calculations. In this data, 18% of men with PSA  $\geq 3$  had a clinically significant prostate cancer when biopsied with SBx. We further

noted that  $rTPF=1.25$  for clinically significant prostate cancer comparing MRI+TBx with SBx based on the results from a meta-analysis (Schoots et al. 2015). We set the noninferiority delta to 4 percentage points for demonstrating noninferiority with respect to sensitivity of clinically significant prostate cancer. We set the alpha to 0.025.

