#### *Updated sample size calculations (performed during Spring and Summer 2019)*

We revised the sample size calculations above in order to have sufficient statistical power to answer comparisons of Stockholm3 vs. PSA within the experimental arm.

The updated, final sample size is the result of a balance between time and financial constraints on one hand and the need to maximise the power for contrasting Strategies 6 vs. 3 on the other hand. In fact, different assumptions about the joint probability of  $ISUP \geq 2$  and screening positive on the PSA test [ $Pr(ISUP \geq 2, PSA \geq 3 \text{ ng/ml})$ ] and about the TPF of the PSA test [ $Pr(PSA \geq 3 \text{ ng/ml} | ISUP \geq 2)$ ] lead to different required sample sizes.

Based on the sample size calculation, we decided to increase the number of men invited into the study to ~50000. Based on an updated estimate of the expected participation rate (25%), this will lead to ~12500 men included in the study and to ~2100 randomised men based on PSA or Stockholm3 (assuming ~16.5% of the enrolled men will test positive on either screening test; 13% passed on PSA alone, leading to ~1600 randomized men with  $PSA \geq 3 \text{ ng/ml}$ ), ~1700 of whom will complete the diagnostic chain, assuming a 20% drop-out rate.

The updated sample size will give:

1. 50–90% power for the contrast S3M+TBx+SBx versus PSA+TBx+SBx. This is based on the following assumptions: 0.015–0.03 probability of detecting  $ISUP \geq 2$  and screening positive on the PSA test (Grönberg et al. 2015), 0.57–0.63 TPF for the PSA test (Thompson et al. 2005),  $rTPF$  (Stockholm3  $\geq 11\%$  vs  $PSA \geq 3$ ) equal to 1 (Grönberg et al. 2015), and a conservative DDR estimate (Alonzo, Pepe, and Moskowitz 2002). The non-inferiority margin was set to  $\delta = -\log(0.78)$  and alpha to 0.025.

Note: the contrast S3M+TBx+SBx versus PSA+TBx+SBx is nested within the experimental study arm, where about 7500 men will be included (due to the 2:3 randomisation). We further assumed a 20% drop-out rate, leading to 6000 men available for the analyses.

| DR_psa | TPR_psa | power |
|--------|---------|-------|
| 0.015  | 0.57    | 0.48  |
| 0.020  | 0.57    | 0.60  |
| 0.025  | 0.57    | 0.70  |
| 0.030  | 0.57    | 0.77  |
| 0.015  | 0.59    | 0.52  |
| 0.020  | 0.59    | 0.64  |
| 0.025  | 0.59    | 0.73  |
| 0.030  | 0.59    | 0.81  |

|       |      |      |
|-------|------|------|
| 0.015 | 0.61 | 0.55 |

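### Between-arm contrasts ignore the Stockholm3 strata used for randomisation: the crude analysis is valid but gives up a modest amount of precision, and the documents disagree on what the strata are

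*Combined protocol and SAP*

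**What the plan says.** **Allocation.** Protocol section 13.3 says "Randomisation will be performed using stratification on disease risk (three strata"), assessed by the Stockholm3 test, and then, in the same section, "Six allocation lists have been created". The SAP's Design section says "Randomization stratified on disease risk [sextiles of the Stockholm3 test] will be used", in blocks of five (two control, three MRI). No text reconciles three strata with six.

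**What the score is.** The SAP's table of independent variables defines the Stockholm3 score as a percentage risk of ISUP ≥2. Its section on missing data describes the score as calibrated to systematic biopsy results and would use it to impute the endpoint.

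**Analysis.** Under Contrasts between study arms, the SAP defines the absolute and relative differences in detection probability (DP) and says of each: "It is estimated by plugging into the formula the observed proportions". The intervals are two-sample Wald intervals with no stratum term. Contrasts 3 vs 1, 2 vs 1 and 9 vs 7 are on the absolute scale; 6 vs 1 and 5 vs 1 are on the ratio scale. Under Additional analyses, covariate models are optional and their covariates are not named. Interaction models serve the subgroup tests. Neither commits to the randomisation strata.

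**The concern.** Stratified, blocked allocation balances the arms on predicted risk of the endpoint. A variance built from pooled proportions still counts the spread in risk between strata as noise. Non-inferiority is decided on the lower confidence limit, so an interval wider than necessary makes a true non-inferiority claim harder to reach. The stratum of every randomised man is already on file, so the missing precision needs no new data.

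The disagreement over strata matters in its own right: an analysis cannot follow the allocation strata, and a reader cannot describe the allocation, until it is clear what they were.

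**Working it through.** **Inputs from the documents.** One-sided alpha: "We set the alpha to 0.025". Absolute margin: "We set the noninferiority delta to 4 percentage points". Ratio margin: 0.78. Control detection 18% in men with PSA ≥3. Planned rDP 1.3 for 3 vs 1. About 1,600 randomised men with PSA ≥3, out of about 2,100 randomised. Dropout 20%, allocation 2:3.

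**Step 1: the plan's own power for 3 vs 1.** 1,600 × 0.8 = 1,280 men, split 512 and 768. Detection 0.18 and 0.18 × 1.3 = 0.234.

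- SE = √(0.18 × 0.82/512 + 0.234 × 0.766/768) = 0.0228
- Power = Φ((0.054 + 0.04)/0.0228 − 1.96) = 98.4%

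The SAP's figure of more than 90% reproduces.

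**Step 2: the stratified variance.** With stratum weights w and stratum detection p, replace p(1−p)/n in each arm by Σ w·p(1−p)/n. Assumptions not in the documents: six strata of equal size among the men analysed, a calibrated logit-normal risk with mean 0.18, and an AUC between 0.60 and 0.80.

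| Assumed AUC | Variance, stratified/crude | Interval narrower by | Half-width, points (crude 4.48) | Power at rDP 1.3 (crude 98.4%) |
|---|---|---|---|---|
| 0.60 | 0.98 | 0.9% | 4.43 | 98.6% |
| 0.65 | 0.96 | 2.2% | 4.38 | 98.8% |
| 0.70 | 0.92 | 4.0% | 4.30 | 99.0% |
| 0.75 | 0.87 | 6.5% | 4.19 | 99.3% |
| 0.80 | 0.81 | 9.9% | 4.03 | 99.5% |

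With three strata the interval narrows by 0.8 to 8.0%.

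**Step 3: smaller true effects.** Assume stratum detection of 5, 8, 12, 17, 24 and 42% (mean 18%). The mean of p² is 0.0477, so the between-stratum part is 0.0477 − 0.18² = 0.0153, or 10% of 0.18 × 0.82 = 0.1476. At rDP 1.0:

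- Crude SE = √(0.1476 × (1/512 + 1/768)) = 0.0219; power = Φ(0.04/0.0219 − 1.96) = 0.45
- Stratified SE = √(0.1323 × (1/512 + 1/768)) = 0.0207; power = Φ(0.04/0.0207 − 1.96) = 0.49

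Simulation of 200,000 trials agrees, and gives 0.75 to 0.79 at rDP 1.1.

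**Step 4: 6 vs 1, the overarching primary contrast.** Completers: 1,700 × 2/5 = 680 and 1,700 × 3/5 = 1,020. Assumed control DP among all randomised men: 0.18 × 1,600/2,100 = 0.137. At a true ratio of 1:

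- SE(log rDP) = √(0.863/(680 × 0.137) + 0.863/(1,020 × 0.137)) = 0.124
- Power = Φ(−ln 0.78/0.1242 − 1.96) = 51.6%

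Stratifying cuts this SE by 0.7 to 7.6% over the same AUC range, giving 52.2 to 58.2%. At a true ratio of 1.25 power moves from 97.9% to 98.0–99.2%. These figures ignore differences in effect between strata.

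**Step 5: error rates.** If 2:3 allocation held exactly within strata among the men analysed, the crude interval would have one-sided error of 2.4 to 1.5% and coverage of 95.2 to 97.0% over the AUC range. A plain stratified Wald interval, simulated at the margin, has one-sided error of 2.7 to 2.8%, against 2.1 to 2.2% for crude.

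**The case against.** The strongest reply is that this is a choice about efficiency, not an error. A simple, prespecified estimator that errs on the conservative side is defensible in a non-inferiority trial. That stands. A reader might infer that the primary analysis is biased or invalid, or that the trial is underpowered because of it. The documents support neither: randomisation makes the crude contrast unbiased, its error rate is below nominal, and at the planned effects of 1.25 to 1.3 power for 3 vs 1 is about 97 to 99% with either analysis.

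It can also be said that the design has not removed all the between-stratum variation from 3 vs 1. Blocks are filled with all randomised men, while 3 vs 1 uses PSA ≥3 completers, 1,280/2,100 = 61% of them. When those men are drawn at random from the blocked set, under the gradient in Step 3, crude coverage is about 95.6% and one-sided error 2.4%. Most of the gain is then ordinary covariate adjustment. This also stands, but the adjustment still gains precision.

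On the strata, six lists agree with sextiles, so the mention of three may be a slip, or there may be an unstated two-level factor. The SAP does credit the scheme with balancing test concordance, which it does not list as a stratification factor. A reader might conclude that men were allocated wrongly; the text shows only that the descriptions differ.

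**Conclusion.** The point holds as a cheap improvement, together with an inconsistency that needs correcting. Each of the five named between-arm contrasts leaves out a stratification factor that the SAP itself uses as a predictor of the primary endpoint. It would be too broad to say this of all between-arm analyses, because the SAP allows model-based ones.

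The direction of the loss is certain; its size is not. It depends on a risk gradient that the documents do not give and on strata of equal size, and the range of 1 to 10% in interval width reflects that. The loss would rarely change the decision on 3 vs 1 at the planned effect. It could matter for 3 vs 1 if MRI detects little more than systematic biopsy, and for 6 vs 1 near equality.

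**What to change.** 1. **Settle the strata.** State once, identically in protocol section 13.3 and the SAP's Design section, the strata on the allocation lists: their number, cut-points and any second factor.
2. **Standardise the primary between-arm estimate.** Estimate the DP in each arm within each allocation stratum, weight by that stratum's share of the analysis set (both arms together), then take the difference or ratio with a matching variance.
3. **Handle 6 vs 1 and 5 vs 1 separately.** Standardise over one common set of randomised men, counting each strategy's detections within it, and form the ratio after standardising. Do not use a common-effect Mantel-Haenszel ratio: Stockholm3-negative men have zero detection under Strategies 5 and 6 by definition, so the ratio is not common across strata.
4. **Guard against the slight anti-conservatism.** Specify an n−1 within-stratum variance or a score-type interval, and check it by simulation at the margin. With about 85 and 128 men per stratum, n−1 raises the variance only by factors of 85/84 and 128/127, about 1%, so it may remove only part of the excess over 2.5%.
5. **Keep crude Wald as a sensitivity analysis.**

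The cost is SAP wording, a little code and the small-sample check. The change must precede any comparative analysis, as the SAP's Preface requires of SAP updates. If comparative results have already been seen, crude should stay primary and the stratified estimate be reported as post hoc.
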